#### Main analysis

The main analyses will be conducted following the intention-to-treat principle. Multilevel modelling (MLM) with restricted maximum likelihood estimation and an unstructured variance–covariance matrix will be used to analyse the main hypotheses on outcome measures. The use of MLM in analysing RCT data has the advantage of accounting for individual differences as a random effect [67–69]. MLM also has advantages over the traditional general linear model approach (e.g. mixed model repeated measures ANOVA) as it is unaffected by randomly missing data and can handle both time-dependent and independent covariates [67, 69]. Missing data for dependent variables will be assumed to be missing at random and accounted for by the maximum likelihood estimation. Two sets of MLMs will be conducted; one will include three treatment arms (CBTI + BLT vs CBTI-BLT vs WL) and two timepoints (pre-treatment vs post-treatment) as fixed effects; the second set will consist of two treatment arms (CBTI + BLT vs CBTI-BLT) and four timepoints (pre-treatment vs post-treatment vs 1-month follow-up vs 6-month follow-up) as fixed effects. The treatment × time interaction will also be included as a fixed effect on both MLMs and will be considered the treatment effect, while repeated measures will be nested within individual participants as random intercepts. A *p*-value of 0.05 represents statistical significance in all analyses. The *p*-values on outcome measures will be adjusted using the Benjamini–Hochberg procedure with a false discovery rate set as 20% to account for multiple comparisons.

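### The outcome model's covariance is described in two ways that do not define one model; the consequence falls mainly on visit-specific contrasts in the four-timepoint active-arm analysis

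*Protocol article*

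**What the plan says.** The protocol article, Statistical analysis, Main analysis, fixes the covariance of the outcome models in two places within one paragraph:

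- "Multilevel modelling (MLM) with restricted maximum likelihood estimation and an unstructured variance–covariance matrix will be used to analyse the main hypotheses on outcome measures"
- "repeated measures will be nested within individual participants as random intercepts"

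It does not say whether the unstructured matrix belongs to the residuals or to the random effects, and it names no random slope. The wording covers two sets of models. The first has three arms and "two timepoints (pre-treatment vs post-treatment) as fixed effects". The second has the two active arms and "four timepoints (pre-treatment vs post-treatment vs 1-month follow-up vs 6-month follow-up) as fixed effects". In both, the treatment × time "interaction will also be included as a fixed effect on both MLMs and will be considered the treatment effect". A p-value "of 0.05 represents statistical significance in all analyses", with a Benjamini–Hochberg "procedure with a false discovery rate set as 20% to account for multiple comparisons". No contrast at a particular visit is named, and no standard deviation or within-person correlation is given.

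**The concern.** The two statements lead to different fitted models. An unstructured residual matrix lets each visit have its own variance and each pair of visits its own covariance. A random intercept with independent residuals imposes one variance and one common correlation at all visits, which is compound symmetry.

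The second model set is where this can matter. Its visits are unevenly spaced (Procedures): Week 0, Week 7, then 1 month and 6 months after the last group session. If correlation falls as visits move apart, compound symmetry averages over pairs that differ. The standard error of the baseline-to-6-month change then comes out too small, and that of changes between adjacent post-treatment visits too large. The hypothesis that effects are maintained at 1 and 6 months (Study objectives) is naturally read through such visit-specific changes. The paragraph applies to all outcome measures, so the affected p-values would also enter the false discovery rate procedure. With two possible models in the text, nobody can tell which one was prespecified.

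**Working it through.** **1. Do the two statements define one model?** With k visits, an unstructured matrix has k(k+1)/2 parameters: 3 for k = 2 and 10 for k = 4.

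- Unstructured residuals plus a random intercept: 3 + 1 = 4 parameters for 3 distinct elements, or 10 + 1 = 11 for 10. Not identified.
- Unstructured random-effects matrix with one intercept: a 1×1 matrix. The word does nothing and the model is compound symmetry (2 parameters).
- Unstructured residuals alone: a valid model, but it contradicts the stated random intercept.

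**2. The plan's own figures.** None concerns the covariance. The sample size of 111 reproduces for a three-group, two-timepoint interaction with f = 0.30/2 = 0.15 and an assumed correlation of 0.5: λ = 0.15² × 111 × 2/(1 − 0.5) = 9.99, power 80.3%. It says nothing about four visits.

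**3. Formula for the random-intercept model (complete data).** Inputs: 48 per arm (Sample size estimation), four visits, two-sided 5% (sidedness assumed). The correlations and SD ratios are assumptions.

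- Residual variance fitted: s² = tr[(I − J/4)Σ]/3, that is, mean variance minus mean covariance.
- SE ratio (model/true) for a change between two visits: r = √(2s²/true variance of the change).
- Degrees of freedom: (96 − 2) × 3 = 282, critical value 1.968.
- Rejection rate under the null: 2·P(t > 1.968·r).

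**4. Worked example.** SD 1 at all visits; correlation 0.7, 0.6 and 0.5 for visits one, two and three apart.

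- Mean correlation: (3 × 0.7 + 2 × 0.6 + 0.5)/6 = 0.633, so s² = 0.367 and 2s² = 0.733.
- Baseline to 6 months: true variance 2(1 − 0.5) = 1.0, r = 0.856, rejection 9.3%.
- Post-treatment to 1 month: true variance 2(1 − 0.7) = 0.6, r = 1.106, rejection 3.0%.

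**5. Range for baseline to 6 months, nominal 5%.**

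| Assumed pattern | Rejection |
|---|---|
| Compound symmetry, equal SDs | 5.0% |
| Compound symmetry, smaller baseline SD | 3.7–4.7% |
| Correlation with baseline 0.4–0.5, later 0.6–0.7 | 6.3–8.9% |
| Linear decay 0.6 to 0.4, or 0.7 to 0.5 | 8.4–9.3% |
| AR(1) by visit order, 0.5–0.8 | 9.2–12.3% |
| Linear decay 0.7 to 0.3 | 12.3% |

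The direction at earlier visits depends on the pattern. For baseline to 1 month, AR(1) by visit order gives 6.9–7.3%, but exponential decay in weeks with correlation 0.7 at 7 weeks gives 3.1%.

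**6. With dropout.** REML random-intercept fits to simulated trials, 4000 per pattern, 48 per arm, random monotone dropout reaching 15%, 22% and 30% at the three later visits: baseline to 6 months 4.6% (compound symmetry) to 11.8%; joint 3-df interaction 4.9–6.6%. The Monte Carlo standard error near 5% is √(0.05 × 0.95/4000) = 0.3 points. Under an unstructured residual matrix, the 6-month contrast rejected 3.0–5.0% in 600 simulated trials per scenario (Monte Carlo standard error 0.9 points), with no inflation.

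**7. Two timepoints.** Here s² = (v₁ + v₂)/2 − c, so 2s² = v₁ + v₂ − 2c, which is the true variance of the change. With complete pairs r = 1 and the test is at 5%.

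**8. The ISI entry cut-off.** Take baseline SD 4, later SD 5, common correlation 0.5. Mean variance (16 + 75)/4 = 22.75, mean covariance (3 × 10 + 3 × 12.5)/6 = 11.25, s² = 11.5. True variance of the baseline-to-6-month change: 16 + 25 − 20 = 21. r = √(23/21) = 1.046, rejection 4.0%: conservative.

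**The case against.** The strongest reply has four parts.

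- **The wording can be reconciled.** Unstructured may be no more than the software option for the random-effects matrix, which can coexist with a random intercept. That is fair, and it makes outright contradiction too strong a description. The word would then be empty, however, and the fitted covariance would not be the one announced. Non-convergence is something a reader might infer, but it would follow only if unstructured residuals and a random intercept were coded together, and the article does not say so.
- **The named test is barely affected.** The treatment effect is defined as the interaction, and its joint test rejects about 5–7%. A reader might quote 7–10% as the plan's error rate. The article does not support that: the figure belongs to a contrast it does not name, and to correlations it does not give.
- **The primary question is untouched.** The ISI comparison with waitlist at end of treatment uses two timepoints. With complete pairs both readings give the same interaction test.
- **An article leaves coding to an analysis plan.** This would excuse silence on covariance. It does not excuse two statements that disagree.

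A reader might also infer that the ISI ≥ 9 entry rule drives the inflation by shrinking the baseline variance. It does not. A smaller baseline SD alone makes the contrast conservative. Carrying the truncation itself through a compound-symmetric normal score (assumed mean 13, SD 5), including the weaker baseline correlation it induces, still gives 4.2–4.6%. Any inflation comes from assumed decay in correlation.

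**Conclusion.** The point stands as a badly fixed specification: the paragraph does not define one covariance model, and no reading makes both statements operative. Its practical reach is the four-timepoint active-arm model behind the secondary maintenance hypothesis.

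Under the random-intercept reading, the unnamed baseline-to-6-month contrast rejects about 4–12% at a nominal 5% across the assumed patterns, above 5% when correlation falls with time and at 5% if compound symmetry holds. Changes between adjacent post-treatment visits are tested too conservatively under decay, with a loss of power. The named joint interaction rejects about 5–7%. These figures assume normal data, 48 per arm and, where dropout was simulated, random dropout of 30%.

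The material does not support a claim that the primary result is compromised. With incomplete pairs the two readings need not agree exactly in the two-timepoint model; that was not quantified. The change is worth making because it is nearly free and settles which analysis was prespecified.

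**What to change.** Replace the two covariance statements under Main analysis with one: visits are repeated measures within participant, with an unstructured residual covariance matrix (2×2 in the first model set, 4×4 in the second), fitted by REML with a small-sample degrees-of-freedom correction such as Kenward-Roger. Delete the reference to random intercepts. This keeps the plan's own choice of an unstructured matrix; within-person dependence is then carried by the residual covariance.

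The cost is the wording and one line of model code. Ten covariance parameters can be estimated from 96 participants at four visits. The small downside is slightly fewer degrees of freedom and an occasional need for a fallback structure if an outcome does not converge, so the fallback should be named in advance.

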### Procedures

Interested individuals can register for the study using an online application form and will be initially screened based on age, ISI score ≥ 9, and rMEQ score ≤ 11. Potential eligible individuals will then be invited to attend a face-to-face clinical interview to ascertain their eligibility for the trial. The diagnoses of sleep disorders and psychiatric disorders will be ascertained using the Diagnostic Interview for Sleep Patterns and Disorders [42] and the Mini International Neuropsychological Interview, respectively [43]. After confirming their eligibility, participants will be randomised to one of the following groups: CBTI + BLT, CBTI-BLT, and WL. Assessments are scheduled at pre-treatment (Week 0), during treatment (Week 2 and Week 4), and post-treatment (Week 7). Assessments at Week 2 and Week 4 will consist of two self-report measures (Insomnia Severity Index and Hospital Anxiety and Depression Scale) for monitoring the clinical status of the participants. Actigraphy will also be used in Week 4 to objectively monitor sleep and circadian-related changes and light exposure across the groups. The two active intervention arms (CBTI + BLT and CBTI-BLT) will be additionally followed up at 1 month and 6 months after the conclusion of the last group session. Participants in the WL group will be offered the treatment (either CBTI + BLT or CBTI-BLT) after completing the post-wait assessment. Figure 1 shows the study flowchart, and the study schedule is summarised in Table 1. Participants will receive HKD 500 (~ USD 64) at the end of the follow-up period as a token of appreciation of their participation in this trial.

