### Measures

#### Primary outcomes

The primary outcome is the change in insomnia symptoms as measured by the Insomnia Severity Index (ISI). The ISI is a seven-item self-rated scale designed to measure one’s insomnia problems, satisfaction with sleep, noticeability and worries towards one’s sleep problems, and insomnia-related interference with daily life. The possible score ranges from 0 to 28, where a higher score indicates greater insomnia severity. The ISI has been validated in local youths demonstrating good construct validity and high internal consistency with a Cronbach’s alpha of 0.83 [40].

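### The pre/post interaction model for ISI is valid but leaves baseline unconstrained, which costs precision, and it omits the Week 2 and Week 4 ISI that could support its missing-at-random assumption

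*Protocol article*

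**What the plan says.** The primary outcome is change in the ISI: "The primary outcome is the change in insomnia symptoms as measured by the Insomnia Severity Index (ISI"). The Main analysis section sets out two multilevel models. The first has three arms and "two timepoints (pre-treatment vs post-treatment) as fixed effects". The second has the two active arms and four timepoints: pre-treatment, post-treatment, 1 month and 6 months. In both, "The treatment × time interaction will also be included as a fixed effect on both MLMs and will be considered the treatment effect". No baseline covariate and no equal-baseline constraint is mentioned.

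On covariance, the section specifies "restricted maximum likelihood estimation and an unstructured variance–covariance matrix" and also that "repeated measures will be nested within individual participants as random intercepts". On missing data: "Missing data for dependent variables will be assumed to be missing at random and accounted for by the maximum likelihood estimation".

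The Procedures section schedules further ISI measurements: "Assessments at Week 2 and Week 4 will consist of two self-report measures (Insomnia Severity Index and Hospital Anxiety and Depression Scale"). It gives their purpose as monitoring clinical status. Neither model includes them. The Sample size section allows for 30% attrition without saying by which visit.

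**The concern.** There are two separate weaknesses.

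The first is precision. Randomisation makes the expected baseline ISI the same in every arm. A model that estimates a separate baseline mean for each arm ignores this, and carries chance baseline differences into the treatment contrast at full weight. Adjusting for baseline, or constraining it to a common mean, removes that noise with data the trial already has.

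The second is missing data. A likelihood analysis is protected under missing at random only with respect to the data it contains. With pre and post values alone, dropout before Week 7 may depend on arm and baseline but not on how the participant was responding. Early response is a plausible reason to leave, and it is measured at Weeks 2 and 4 but left out of the model.

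**Working it through.** **Inputs from the protocol.** Three arms, 48 per arm, 30% attrition, g = 0.30 to 0.47, alpha 0.05, power 80%, N = 111 before attrition, entry at ISI of 9 or more. **Assumed, because not given.** Pre-post correlation r, ISI SDs, timing of dropout and dropout mechanism.

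**1. The plan's own figure.** Take a three-arm, two-timepoint interaction F test with f = g/2 = 0.15 and r = 0.5. The noncentrality is f² × N × 2/(1 − r) = 0.0225 × 111 × 2/0.5 = 9.99, on 2 and 108 degrees of freedom. Power is 0.803, so 111 is reproduced. With two timepoints this test is a one-way comparison of change scores, which agrees with reading the planned model that way. The match is not unique: four timepoints with r = 0.3 also give 111.

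**2. Complete data, equal SDs.** Variance per participant, in units of the post-treatment variance, is 2(1 − r) for the change score and 1 − r² for the baseline-adjusted analysis.
- r = 0.3: 1.40 against 0.91, an excess of 54%.
- r = 0.5: 1.00 against 0.75, an excess of 33%.
- r = 0.7: 0.60 against 0.51, an excess of 18%.

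**3. Complete data, truncated baseline.** Let the baseline SD be 0.7 of the post-treatment SD, with r = 0.4. Change: 0.49 + 1 − 2 × 0.4 × 0.7 = 0.93. Adjusted: 1 − 0.16 = 0.84. The excess is 11%.

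**4. With 30% missing at Week 7, r = 0.4.** The planned model's variance is the residual variance divided by 0.7, plus (b − 1)² × baseline variance, where b is the slope of post on baseline. The common-baseline model drops the second term.
- Equal SDs (b = 0.4): 0.84/0.7 + 0.36 = 1.56 against 1.20, an excess of 30%. A completers-only change score would give 1.20/0.7 = 1.71.
- Truncated baseline (b = 0.4/0.7): 0.84/0.7 + 0.09 = 1.29 against 1.20, an excess of 7.5%.

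**5. In power terms.** At 48 per arm, 30% missing, r = 0.5 and equal SDs, the standard error of a pairwise contrast is √((0.75/0.7 + 0.25) × 2/48) = 0.235 as planned and √((0.75/0.7) × 2/48) = 0.211 with a common baseline. Pairwise power at g = 0.47 is 0.52 and 0.60.

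**6. What Weeks 2 and 4 add to precision.** Assume correlations of 0.50, 0.45 and 0.40 between baseline and Weeks 2, 4 and 7, then 0.70 (2 with 4), 0.55 (2 with 7) and 0.70 (4 with 7). Assume 15% are last seen at Week 4, 10% at Week 2 and 5% at baseline. The common-baseline variance falls from 1.20 to 1.09. Since √(1.09/1.20) = 0.95, that is about 5% in the standard error. At r = 0.5 with other assumed correlation patterns and staggered dropout, the gain was about 2 to 3%.

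**7. What they add to the missing-data assumption.** Simulation with 400,000 per arm, true effect −0.60 SD, about 30% dropout in the active arm, and dropout logistic in Week 4 ISI:
- Response-driven dropout in the active arm only, unrelated dropout in waitlist: the pre/post model gives about −0.74, and adding Weeks 2 and 4 gives −0.60.
- The same rule in both arms, relative to each arm's own mean: the pre/post model gives −0.60.
- The same absolute ISI rule in both arms: the pre/post model gives about −0.56.

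A second illustration (SD 5, true effect −4 points, response-driven dropout in the active arm only) gave −4.33 to −4.55 for pre/post, and −4.00 to −4.01 with Weeks 2 and 4.

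**The case against.** The arm-by-time interaction is a standard analysis, is unbiased under randomisation, and matches a plausible basis for the sample size. That stands, so the baseline point is one of efficiency. The equal-SD figures are also the favourable case. The entry rule truncates baseline ISI, and the gain may then be under a tenth of the variance. Under dropout the likelihood keeps participants who have only a baseline value, so the planned model does somewhat better than a completers-only change score (1.56 against 1.71).

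The protocol declares the Week 2 and Week 4 ISI to be for monitoring, and its hypotheses concern the end of treatment. This makes the omission a design choice. It explains why the data are collected, but it does not make missing at random more credible without them.

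Three stronger readings are tempting, and the document does not support them.
- *The treatment effect will be overstated if poor responders leave.* The simulations show overstatement, no bias or understatement according to how dropout differs between arms, and nothing in the protocol indicates which applies. The 30% is not tied to Week 7 and may include loss up to 6 months.
- *The covariance is mis-specified.* An unstructured 2 × 2 residual matrix already has all three parameters, so adding a random intercept would not be identifiable. But in a multilevel model the term can describe the random-effects matrix. The result is then compound symmetry, which is valid and, with two visits and complete data, gives the same contrast and standard error. The wording is ambiguous, which is not the same as wrong.
- *The Week 2 and Week 4 data exist for everyone.* Table 1 marks the ISI under treatment but leaves the waitlist row blank in that column, and the abstract mentions only baseline and post-treatment for all participants. The Procedures section lists the interim visits before singling out the active arms for follow-up, which suggests all arms but does not say so.

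**Conclusion.** The point holds as a weakness in efficiency and in the support for missing at random. The planned contrast is neither invalid nor contradicted elsewhere in the protocol. The avoidable variance is 18 to 54% with complete data, equal SDs and r between 0.7 and 0.3. With a baseline SD of 0.7 of the post-treatment SD and r = 0.4, it is about 11% with complete data and 7.5% with 30% missing. The correlation and SDs are assumptions throughout. Most of the recoverable precision comes from handling baseline: in the equal-SD example 0.36 of the 0.47 reduction from 1.56 to 1.09, where the interim visits supply the other 0.11. The interim visits matter mainly because they let early response inform the handling of dropout. Any bias from leaving them out is conditional on an arm-specific mechanism, and its size and sign cannot be predicted from the document.

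**What to change.** - Estimate the Week 7 ISI contrasts of each active arm against waitlist with baseline ISI as a covariate interacting with visit, or with a baseline mean constrained to be common across arms. Use the same form for the other outcomes and for the two-arm follow-up model.
- State whether the waitlist completes the ISI and HADS at Weeks 2 and 4. If all three arms do, add these visits as outcomes with arm-by-visit terms. If the waitlist does not, use them in the active arms only, for example through arm-specific imputation.
- Name one covariance structure: unstructured residual covariance across visits, with no participant random intercept.

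This needs analysis wording and code, and no additional assessments.

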### Randomisation and masking

Randomisation will be completed using simple randomisation with a 1:1:1 allocation ratio. A pre-randomised list with random sorting of the three trial arms will be generated in Microsoft Excel using the = RAND() function. As each participant enrols in the study, he/she will be sequentially assigned to the corresponding group in the pre-randomised list. The entire randomisation procedure will be completed by a trained research assistant who is not involved in other aspects of the trial. The project therapists and clinical assessors will be blinded to the group allocation. We do not anticipate any requirement for unblinding but if required, the Trial Manager, Data Coordinator, and Implementation Support Facilitators will have access to group allocations and any unblinding will be reported.

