### Intervention

#### Cognitive behavioural therapy for insomnia

The CBT-I programme consists of six weekly sessions, 90 min each. The sessions will be conducted in a group format (four to six participants per group) and facilitated by trained therapists. The group sessions are structured and adopted from a well-established protocol for treating insomnia with additional emphasis on the effect of the circadian rhythm [57]. The programme aims to address the behavioural, cognitive, and physiological factors perpetuating insomnia. Table 4 summarises the session content of the CBT-I programme.

**Table 4 Tab4:** Summary of the CBT-I programme

Session	Topics
1	• Programme overview • Psychoeducation on normal sleep, circadian rhythm, and insomnia • Introduction to 3Ps model of insomnia and case formulation • Introduction to the use of a sleep diary
2	• Review of sleep diary • Introduction to bright light therapy using Re-Timer • Behavioural strategies (sleep restrictions, stimulus control) • Sleep hygiene education • Setting sleep windows
3	• Review of sleep diary and use of Re-Timer and adjustment of sleep windows • Introduction to different treatment approaches for insomnia • Stress management and relaxation exercises • Constructive worry techniques
4	• Review of sleep diary and use of Re-Timer and adjustment of sleep windows • Cognitive restructuring Part I
5	• Review of sleep diary and use of Re-Timer and adjustment of sleep windows • Cognitive restructuring Part II
6	• Review of sleep diary and use of Re-Timer and adjustment of sleep windows • Review of the programme • Consolidating gains and relapse prevention

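### CBT-I is delivered in groups in the two active arms, but the stated model has no therapy-group term, so standard errors against waitlist are too small if outcomes correlate within groups

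*Protocol article*

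**What the plan says.** On delivery, the Protocol article (Cognitive behavioural therapy for insomnia) states: "The sessions will be conducted in a group format (four to six participants per group) and facilitated by trained therapists". Both active arms receive this programme. Under Procedures and Table 1, the waitlist is offered treatment only after its post-wait assessment.

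On allocation, Randomisation and masking states: "Randomisation will be completed using simple randomisation with a 1:1:1 allocation ratio". Participants are assigned one by one as they enrol, so therapy groups are formed after randomisation and are not the unit randomised. The same section adds: "The project therapists and clinical assessors will be blinded to the group allocation". Nothing says whether a therapy group contains one active arm or both.

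On analysis, Main analysis specifies "Multilevel modelling (MLM) with restricted maximum likelihood estimation and an unstructured variance–covariance matrix". Of the two sets of models, "one will include three treatment arms (CBTI + BLT vs CBTI-BLT vs WL) and two timepoints (pre-treatment vs post-treatment) as fixed effects"; the other compares the two active arms over four visits. "The treatment × time interaction will also be included as a fixed effect on both MLMs and will be considered the treatment effect". The random part is described as "repeated measures will be nested within individual participants as random intercepts". Neither therapy group nor therapist appears in it. Sample size estimation gives no ICC and no design effect.

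**The concern.** Members of one therapy group share sessions, a therapist and each other's company for six weeks, so their outcomes after treatment may be more alike than those of participants from different groups. The waitlist has no such source of similarity before its post-wait assessment. This is a partially nested design: clustered in two arms, unclustered in the third.

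The stated model treats all participants as independent. The unstructured matrix does not help, because it describes correlation between repeated measures on one participant and not between participants. With a positive within-group correlation, the variance of an active-arm mean is understated, intervals against waitlist are too narrow and p-values too small. This touches the primary outcome (ISI) and every secondary outcome analysed with the same models. Those p-values then enter the Benjamini–Hochberg step, which takes them as valid.

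**Working it through.** **The plan's own figure.** The 111 evaluable participants reproduce as a one-way ANOVA F test on three groups of 37 with Cohen's f = 0.30 and alpha 0.05 (power 0.803). That calculation assumes independent participants, so clustering is absent from the sample size as well as from the model. (The article labels the 0.30 as Hedges' g; that is a separate matter.)

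**Inputs.** Group size of 4 to 6, taken as m = 5, or 5 × 0.7 = 3.5 after the 30% attrition in Sample size estimation. ICC: not in the article; assumed 0.02 to 0.10, and applied to the change from baseline because the treatment effect is the arm-by-time interaction.

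**Arm-specific groups.** The variance of an active-arm mean is multiplied by D = 1 + (m − 1) × ICC. The contrast of an active arm with waitlist has variance factor (1 + D)/2, since only one side is clustered. The contrast between active arms has factor D. A nominal two-sided 5% test has actual error 2[1 − Φ(1.96/√factor)].

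| m | ICC | D | (1 + D)/2 | Error vs waitlist | Error between active arms |
|---|---|---|---|---|---|
| 3.5 | 0.02 | 1.05 | 1.025 | 5.3% | 5.6% |
| 3.5 | 0.10 | 1.25 | 1.125 | 6.5% | 8.0% |
| 5 | 0.02 | 1.08 | 1.04 | 5.5% | 5.9% |
| 5 | 0.05 | 1.20 | 1.10 | 6.2% | 7.4% |
| 5 | 0.10 | 1.40 | 1.20 | 7.4% | 9.8% |

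At m = 5 and ICC 0.05, the correct standard error against waitlist is √1.10 = 1.05 times the one the model reports. Full groups of 6 with ICC 0.10 would give 8.0% against waitlist and about 11% between active arms. At m = 5 and ICC 0.01 the figure against waitlist is 5.2%.

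**Mixed groups.** With m = 5 split evenly, each arm has 2.5 members per group.
- ICC 0.05: D = 1 + 1.5 × 0.05 = 1.075, factor 1.0375, error 5.4%.
- ICC 0.10: D = 1.15, factor 1.075, error 5.9%.

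Uneven splits raise these a little. Between the active arms the shared group effect largely cancels; with an exactly even split the variance factor is 1 − ICC, which is below 1.

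**Simulation.** Change scores were simulated under no treatment effect with 50 per arm (the Abstract's 150 divided by three) and m = 5. They were analysed with an ordinary two-sample t test over 8,000 runs, giving a Monte Carlo standard error of about √(0.05 × 0.95/8000) = 0.24 percentage points.

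| ICC | vs waitlist, arm-specific | between arms, arm-specific | between arms, mixed |
|---|---|---|---|
| 0.01 | 5.3% | 5.0% | 4.8% |
| 0.05 | 6.5% | 7.8% | 5.2% |
| 0.10 | 7.4% | 10.6% | 4.9% |

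The simulation agrees with the formulas.

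**Power.** Applying D to the two active arms only (m = 5, arm-specific), 37 × D rounded up gives 39, 45 and 52 per active arm at ICC 0.01, 0.05 and 0.10. With 37 on waitlist the evaluable total is 2 × 39 + 37 = 115, 2 × 45 + 37 = 127 or 2 × 52 + 37 = 141, against 111.

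**The case against.** **No ICC is given.** A reader might infer that the standard errors are certainly too small. The article does not support that: the inflation needs a positive within-group correlation, and at 0.01 it is negligible. The omission is certain; its size is not. Moreover, the ICC that matters is the one for change from baseline. It differs from the ICC of post-treatment scores by an amount that depends on the pre–post correlation, which is also not given.

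**Groups may be mixed.** A reader might take 9.8%, or a count of about ten groups per active arm (48/5 = 9.6), as the expected situation. Both presuppose arm-specific groups. The article says therapists are blinded, both arms wear a Re-Timer, Table 4 describes one common programme, and light timing is reviewed individually. Mixed groups are therefore possible, and then the active-arm contrast is not inflated and the waitlist inflation shrinks. This stands.

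**The worst figure is not for a primary contrast.** The first two primary hypotheses compare with waitlist, where the range is lower. This also stands, although the second set of models tests the active-arm contrast directly.

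**An unseen analysis plan might add the term.** The article condenses a fuller protocol and does not say that the participant intercept is the only random effect. But Main analysis goes beyond a summary: it names the estimator, the covariance, the fixed effects and the nesting level, and omits the level that group delivery creates. Followed as written, the model ignores it. This objection tempers the tone but does not remove the point.

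**Conclusion.** The point holds in conditional form. The stated model omits therapy-group clustering that the intervention creates in two of three arms. Under any positive within-group correlation, it understates the standard errors of the active-versus-waitlist contrasts, whether groups are arm-specific or mixed. Under the assumed ICCs the inflation against waitlist is modest: at most 7.4% for a nominal 5% test with groups of up to 5, and less if groups are mixed. The larger figures for CBTI + BLT versus CBTI-BLT apply only if groups are arm-specific, which the article does not state. That conditionality, and the size for the primary contrasts, make this a should-fix and not a flaw that by itself invalidates the primary analysis.

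**What to change.** State whether therapy groups are arm-specific or mixed, and record a therapy-group identifier for every treated participant. Add to both sets of models a therapy-group random effect that acts only at post-randomisation visits in the active arms. Each waitlist participant is a singleton, and if groups are mixed the same identifier is shared across arms. Use Kenward–Roger or Satterthwaite degrees of freedom, because with arm-specific groups 48 per arm gives only 8 to 12 groups per active arm (48/6 to 48/4). Report the estimated ICC.

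The cost is one variable and one variance component, slightly wider intervals and some loss of power, as the evaluable totals above show. With few small groups the group variance may be estimated at or near zero. The plan should say in advance what is done then, so that dropping the term does not become a choice made after seeing the result.
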